### Sample Size

This trial aims to objectively assess the efficacy and safety of RZZYL for CHE through a high-quality clinical study design, thereby providing substantial data support for medication development and translation. The trial uses mometasone furoate cream as the positive drug control, categorizing it as a noninferiority trial. According to pertinent literature, the efficacy rate of mometasone furoate cream for treating HE, as assessed by the symptom improvement index using the Nimodipine method, is 53% [21]. Based on previous clinical observations, the efficacy rate for the RZZYL (granules) group is 73.47% [22]. Using the noninferiority study formula (equation 1) [23], with a statistical power (1-β) set at .9, an alpha level (α) of .025, and a noninferiority margin (δ) of 0.095 [24], the values for z_α_ and z_β_ are 1.95996 and 1.28155, respectively, with k (prespecified noninferiority margin) set to 1. The symbol “z” typically represents the critical value in a standard normal distribution, used to calculate the critical region in hypothesis testing. The sample size calculation indicates that the control group requires approximately 53 participants (n_c_). Consequently, the sample size for the experimental group (n_t_) is calculated as k×n_c_=53 participants, leading to a total sample size of 106 participants. Considering an anticipated attrition rate of 15.0% [25], the necessary sample size is adjusted to 61 participants for both the control and experimental groups, resulting in a total required sample size of 122 participants.

(1)
$$n_{c}=\frac{\left(Z_{1-\alpha }+Z_{1-\beta }{)}^{2}\cdot [P_{C}(1-P_{C})+P_{T}(1-P_{T})\right]}{(P_{C}-P_{T}-\delta {)}^{2}}$$

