### Randomization, Concealment, and Blinding

This study will use the SAS (SAS Institute) PROC PLAN process statement to generate random numbers to determine the seed number and fragment length. The treatment tasks corresponding to run numbers 001‐120 will be documented. To ensure allocation concealment, the randomization process will be overseen by an independent statistician who is not involved in the study [28]. Eligible participants will be randomly assigned to either the treatment or control groups in a 1:1 ratio. The random numbers will be placed in a closed, opaque envelope, secured in our center. To ensure objectivity, operators will not be aware of any evaluations by efficacy evaluators and vice versa. Only the operators will have access to the random numbers prior to the commencement of the treatment. Further, they are not going to take part in the evaluation. To maintain strict allocation concealment, the system shall log metadata, such as time of randomization, operator’s identity, and IP address. The quality control will regularly check these logs for any violations or deviations. In order to blind the participants, both groups will receive the same package of drug and placebo, with a similar treatment protocol. The placebo will add artificial coloring to ensure size, color, shape, taste, odor, and packaging are all identical to the active drug. Unblinding will occur only after the completion of case collection. However, an emergency unblinding procedure may be initiated if a serious adverse event or urgent medical treatment is necessary during the study.

Furthermore, the quality control team will conduct anonymous surveys at 3 critical stages, including when the trial reaches (1) 50% completion, (2) just before its conclusion, and (3) before unblinding. These surveys will evaluate whether participants, clinical researchers, and efficacy evaluators are aware of the group allocations. The data collected from these surveys will be subjected to statistical analysis to mitigate the risks of performance and detection biases, thereby enhancing the study’s credibility.

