#### Investigator Global Assessment

Researchers and clinicians use the Investigator Global Assessment (IGA) score to gauge a patient’s skin condition. The score is often used in clinical trials for eczema and other skin diseases. Rating the severity of a disease depends on the characteristics of skin lesions, such as redness, exudation, and thickness. The dermatological revised scoring system works on a 5-point scale, ranging from 0 to 4, where higher scores indicate more severe skin conditions.

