### Data Analyses

The results of this trial will be analyzed from three perspectives:

Full Analysis Set (Intention-to-Treat Analysis): This set includes all randomized participants, with data analyzed according to the principle of “randomization equals analysis.” Missing data will be addressed using multiple imputation methods. Predictive mean matching will be used for continuous variables while logistic regression imputation will be used for categorical variables.Per Protocol Set: This set comprises participants who meet specific criteria; that is, they must have completed at least 80% of the treatment regimen (ie, a minimum of 22 days of medication within 4 weeks), have not used prohibited study drugs, and possess complete data for the primary end point (HECSI score).Safety Set: This set includes all participants who received at least 1 dose of the study medication.

The variable processing and statistical methods for this trial are outlined as follows: (1) continuous variable data that adhere to a normal distribution will be presented as mean (SD). Independent sample *t* tests (2-tailed approach) will facilitate between-group comparisons while repeated measures ANOVA will be applied for comparisons across multiple time points (eg, baseline, during treatment, and post treatment); (2) data that do not conform to a normal distribution will be expressed as median (IQR), with between-group comparisons executed using the Mann-Whitney *U* test; (3) categorical data will be described in terms of proportions or percentages, with between-group comparisons conducted using chi-square tests or Fisher exact test, depending on the final sample size. (4) All data processing and chart generation will be performed using R 4.0 software (R Project for Statistical Computing). Statistical tests will be 2-sided, with a significance level at *P*<.05.

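### The protocol has no analysis rule for the ordered 0–4 IGA, so it can be read as sending this secondary outcome to a test that ignores the order of the grades

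*Protocol article*

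**What the plan says.** The section Investigator Global Assessment, under Secondary Outcomes, describes an ordered grade: "The dermatological revised scoring system works on a 5-point scale, ranging from 0 to 4, where higher scores indicate more severe skin conditions". The Abstract lists the IGA among four secondary outcomes, assessed at baseline and at weeks 2 and 4.

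Data Analyses sorts variables by type and names the tests for each:

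1. Normally distributed continuous variables: *t* tests and repeated measures ANOVA.
2. Data that are not normally distributed: medians with IQRs, and a Mann-Whitney comparison of the arms.
3. For anything classed as categorical, the rule reads: "categorical data will be described in terms of proportions or percentages, with between-group comparisons conducted using chi-square tests or Fisher exact test".

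Missing data in the full analysis set are handled by multiple imputation, split two ways: "Predictive mean matching will be used for continuous variables while logistic regression imputation will be used for categorical variables".

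The article does not say which of the three rules, or which imputation method, applies to the IGA. It names no ordinal model or trend test and defines no IGA responder cut.

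**The concern.** Of the six efficacy outcomes, HECSI, POEM and DLQI are multi-item totals, the itch NRS is a 0–10 score and target lesion area is a percentage reduction. The IGA is the only single graded category, so a reader looking for the outcome that rule 3 is meant for would naturally pick it.

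On a 2×5 table, a chi-square or Fisher exact test gives the same *P* value however the five grades are relabelled. It spreads its sensitivity over any difference in pattern (4 degrees of freedom for the chi-square), and a significant result does not by itself show which arm did better. The Sample Size section describes a noninferiority trial, in which direction matters.

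Rule 2 would keep the order. The two readings therefore lead to tests of materially different power on the same data, and the text leaves room to choose between them after the data are seen.

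**Working it through.** **Inputs from the protocol article.** Five ordered levels, 0–4 (Investigator Global Assessment). Two-sided tests at .05 (Data Analyses). Allocation 1:1 (Randomization, Concealment, and Blinding). 53 evaluable and 61 randomized per arm, with efficacy rates of 53% and 73.47% (Sample Size).

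**Inputs assumed.** The week 4 IGA distribution in the control arm and the size of the treatment effect. The document gives neither, so a range is shown.

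**The plan's own figure.** Equation 1 gives (1.95996 + 1.28155)² × [0.53×0.47 + 0.7347×0.2653] / (0.53 − 0.7347 − 0.095)² = 51.94, so 52 per arm against the stated 53. This agrees to within one patient. It concerns a binary efficacy rate and does not involve the IGA.

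**One worked case.** Take control grades 0–4 as 15/30/30/20/5% and a common odds ratio of 2.5 in favour of the treated arm.

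- Control cumulative proportions .15, .45, .75, .95 have odds .176, .818, 3, 19.
- Multiplying by 2.5 gives .441, 2.045, 7.5, 47.5, hence treated cumulative proportions .306, .672, .882, .979.
- The treated grades are therefore 30.6/36.6/21.1/9.7/2.1%.
- The chi-square noncentrality with *n* per arm is *n* × Σ(p_C − p_T)²/(p_C + p_T) = 53 × (.0534 + .0065 + .0156 + .0357 + .0122) = 53 × .1234 = 6.54.
- On 4 degrees of freedom, 6.54 gives power of about 51%. If the whole signal were carried on 1 degree of freedom, which a test for an ordered shift approximates, the same 6.54 would give about 72%.
- Simulation (20,000 trials) agrees: 49.5% for the 2×5 chi-square and 72.9% for the tie-corrected Mann-Whitney test, a difference of 23.4 points.

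**Range over assumptions.** Five control distributions (the one above, a uniform one and three others), proportional odds, 20,000 simulated trials per scenario. Entries are the points of power by which the 2×5 chi-square falls below Mann-Whitney:

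| Odds ratio | 53 per arm | 61 per arm |
|---|---|---|
| 1.5 | 7.0–9.5 | 8.5–10.6 |
| 2.0 | 15.9–21.0 | 17.0–21.8 |
| 2.5 | 18.4–23.8 | 17.7–22.4 |
| 3.0 | 15.7–19.7 | 13.7–17.6 |
| 3.5 | 11.7–15.0 | 8.8–11.5 |

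With no effect (odds ratio 1), both tests reject in about 4% to 5% of trials, so the difference is not bought with excess type I error.

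**A second set.** Suppose the planning rates were the proportions at IGA 0–1. The odds ratio is then (0.7347/0.2653)/(0.53/0.47) = 2.46. Four control distributions were tried, each with 53% at grades 0–1: 20/33/27/15/5, 10/43/30/14/3, 25/28/25/17/5 and a four-level 18/35/32/15. With 6,000 simulated trials each and 53 per arm, chi-square power was 48.6, 44.5, 49.0 and 53.4% against 72.2, 69.5, 70.9 and 70.4% for Mann-Whitney, differences of 23.6, 25.0, 21.9 and 17.0 points.

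Together the two sets give roughly 7 to 25 points.

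**The case against.** The strongest reply is that the document never places the IGA under rule 3. It calls the IGA a score, and rule 2 is worded for data in general rather than only for continuous variables, so a 0–4 score fits it readily. On that reading the plan already names a test that uses the order, and the power loss is zero. This stands, and it is why the point concerns an unsettled choice and not a wrong test already fixed.

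A reader might go further and infer that the plan commits the IGA to chi-square or Fisher and so loses a known amount of power. The documents do not support that. No sentence makes the assignment. The planning rates are not IGA rates either: the control figure is an efficacy rate "as assessed by the symptom improvement index using the Nimodipine method, is 53"%. Nor can one figure be given for a collapsed IGA, because no cut is defined. In the simulations a 0–1 versus 2–4 split lost about 0.5 to 18 points and a 0 versus 1–4 split about 3 to 50.

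A reader might also infer that logistic regression imputation must collapse the grades or discard their order. The article does not state the form, and a proportional-odds logistic imputation would fit the same words. What can be said is that the form is open.

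Two further replies have weight. Rule 3 reports proportions by arm, so the direction would be visible descriptively even beside an unordered test. And an article may leave the assignment of each secondary scale to an analysis plan that is not shown. The second reply limits the weight of the point but does not remove it: the article does state a rule for categorical data, without excepting ordered grades, and that rule suits this outcome poorly if applied.

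**Conclusion.** The concern holds in a conditional form. The IGA is an ordered five-level grade, the Data Analyses section has no rule for ordered categories, and two of its rules can be read to cover the IGA. Under the categorical rule on the full 2×5 table, power is roughly 7 to 25 points below that of a rank test. This assumes proportional odds, odds ratios between 1.5 and 3.5, illustrative control distributions and 53 or 61 patients per arm. Under the Mann-Whitney rule the loss is zero.

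The IGA is a secondary outcome. HECSI, the itch NRS and the sample size do not depend on this point. It is worth correcting because the correction costs almost nothing and removes a choice that could otherwise be made after the data are seen.

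**What to change.** Amend Data Analyses, before unblinding, in three places:

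- Limit rule 3 to binary and unordered categorical data.
- State that week 4 IGA is analysed on all five levels with a proportional-odds model containing treatment and baseline IGA, reporting the common odds ratio with its 95% CI. At the least, assign the IGA by name to the Mann-Whitney test already in rule 2, with tie correction. The proportion at each grade can still be tabulated.
- State that missing IGA values are imputed by ordinal (proportional-odds) logistic imputation or by predictive mean matching.

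This takes a few sentences and no extra patients or data, since baseline IGA is already collected. The small downside is that the common odds ratio rests on the proportional-odds assumption; the Mann-Whitney alternative does not need it.

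### The trial is declared and sized as noninferiority on an efficacy rate, but that rate is not a listed outcome and the stated tests use no margin, so the 90% power does not apply to the stated analysis

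*Protocol article*

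**What the plan says.** - **Design (Sample Size):** "The trial uses mometasone furoate cream as the positive drug control, categorizing it as a noninferiority trial".
- **Quantity sized on (Sample Size):** for the control arm, "the efficacy rate of mometasone furoate cream for treating HE, as assessed by the symptom improvement index using the Nimodipine method, is 53"%; for the experimental arm, "the efficacy rate for the RZZYL (granules) group is 73.47"%. The margin is 0.095, a difference in proportions. The error rates are "an alpha level (α) of .025" and "with a statistical power (1-β) set at .9". The result is 53 per arm, raised to 61 per arm (122 in total) for 15% attrition.
- **Outcomes (Abstract, Primary Outcomes, Secondary Outcomes):** the primary outcomes are the HECSI and itch NRS scores. The secondary outcomes are target lesion area, POEM, DLQI and IGA. No efficacy rate is listed and no response cut-off is given. The Per Protocol Set definition in Data Analyses treats the HECSI score alone as the primary end point.
- **Tests (Data Analyses):** two-tailed t tests, repeated measures ANOVA, Mann-Whitney U, and chi-square or Fisher tests, assigned by type of variable. "Statistical tests will be 2-sided, with a significance level at" P<.05. The section mentions no margin, noninferiority hypothesis or confidence interval.

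**The concern.** A noninferiority claim needs three things to match: the endpoint, a margin on that endpoint's scale, and an analysis that compares the estimate's uncertainty with the margin. Here the margin belongs to a proportion that is not an outcome. The outcomes are scores that have no margin. The tests named all have zero difference as their null hypothesis.

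Two things are at stake. First, the plan as written contains no rule by which the trial could conclude noninferiority to mometasone, which is its declared purpose. Second, the only power figure given describes a test that is not in the analysis section. If the endpoint, cut-off and margin scale are settled only after unblinding, the choice will be open to the charge that the data drove it.

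**Working it through.** **1. Reproduce the plan's figure.** Inputs from Sample Size: P_C = 0.53, P_T = 0.7347, δ = 0.095, z = 1.95996 and 1.28155.

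n = (1.95996 + 1.28155)² × [0.53×0.47 + 0.7347×0.2653] / (0.53 − 0.7347 − 0.095)²

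= 10.507 × 0.4440 / 0.08982 = 51.94

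This rounds up to 52, against the stated 53. Then 53 × 1.15 = 60.95, so 61 per arm. The 90% power therefore belongs to a one-sided .025 noninferiority test of two proportions with margin 0.095.

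**2. Set the sections side by side.**

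| | Sample Size | Outcome sections | Data Analyses |
|---|---|---|---|
| Quantity | Efficacy rate | HECSI and NRS scores | Methods by variable type |
| Margin | 0.095 (proportion) | None | None |
| Null hypothesis | RZZYL worse by the margin or more | – | No difference |

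A margin of 0.095 on a proportion has no meaning on a 0–10 itch scale or a HECSI total.

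**3. Check the alpha level.** Requiring the lower limit of a two-sided 95% CI to exceed the margin is a one-sided .025 test. Two-sided .05 in one section and .025 in the other are compatible.

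**4. Power of the noninferiority test that was sized, 53 per arm, control rate 53%.** Power = Φ[(P_T − P_C + 0.095)/SE − 1.96], with SE = √{[P_C(1−P_C) + P_T(1−P_T)]/53}.

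| True P_T | Advantage | SE | Power |
|---|---|---|---|
| 0.7347 | +20.5 points | 0.0915 | 90.6% |
| 0.63 | +10 points | 0.0954 | 53.4% |
| 0.53 | 0 | 0.0970 | 16.4% |

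At equal rates, 90% power would need 10.507 × 2 × 0.2491 / 0.095² ≈ 580 per arm.

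**5. Power of the score tests.** The protocol gives no SD and no expected score difference, so this cannot be derived. Under an assumed standardised difference, a two-sided .05 t test with 53 per arm has about 34% power at 0.3 SD and 73% at 0.5 SD. It reaches 90% at (1.95996 + 1.28155) × √(2/53) = 0.63 SD.

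**6. Illustration only: a two-sided chi-square test on the Sample Size rates.** The protocol does not plan this test.
- At 53% v 73.47%, power is about 59% with 53 per arm (65% with 61).
- With RZZYL truly 9.5 points worse (43.5%), the test is non-significant about 83% of the time (83.4% with unpooled variance, 83.6% with pooled).
- With RZZYL 15 points worse (38%), it is non-significant about 66% of the time (65.2% unpooled, 66.0% pooled).

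**The case against.** The strongest defence is that this is a condensed article. The CI method, the decision rule in each analysis set and a switch to superiority are commonly left to a full protocol or SAP. That is fair, and the absence of such detail is no finding. But the article is not silent here: it states the outcomes, the tests and their null hypothesis, and these do not match the design it declares.

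A reader might infer more than the documents support in five ways:

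- **That only score tests are planned.** Data Analyses assigns methods by variable type and includes chi-square and Fisher tests. These are still difference tests without a margin, and no responder outcome is defined for them.
- **That the planned chi-square test has 59% power instead of 90%.** No chi-square test of the efficacy rate is planned, so the 59%, 83% and 66% figures only illustrate.
- **That .05 in the analysis contradicts .025 in the sizing.** It does not, as step 3 shows.
- **That the sponsor will read P>.05 as equivalence.** Nothing in the protocol says so.
- **That the two source rates are not comparable.** They come from separate references that cannot be examined here. The document ties the Nimodipine method only to the 53%, so a common definition is unconfirmed but not disproved.

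It may also be said that a significant result favouring RZZYL would make noninferiority moot. On the efficacy rate it would, but that outcome is not listed. Short of superiority, no stated rule permits the noninferiority conclusion.

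**Conclusion.** The point holds as a contradiction between stated parts of the protocol. The declared hypothesis and its margin concern an efficacy rate that is not an outcome, and the stated tests compare nothing with any margin. Noninferiority is therefore not tested by the analysis as written, and the stated 90% power does not apply to it. The fault lies in the endpoint mismatch and the missing margin comparison, not in the alpha level. This should be corrected before unblinding.

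The size of the problem for the HECSI and NRS tests is unknown, because the protocol gives no SD or score difference. For the noninferiority test that was sized, 90% power is conditional on a true 20.5-point advantage. It falls to about 53% at 10 points and 16% at equality, assuming a 53% control rate, 53 evaluable patients per arm and the normal approximation.

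**What to change.** Before unblinding, reconcile the Abstract, Sample Size, Primary Outcomes and Data Analyses by one of two routes.

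**(a) Make the Sample Size efficacy rate the primary noninferiority endpoint.** State the scale and response cut-off, and confirm that both the 53% and the 73.47% rest on that definition. Declare noninferiority if the lower limit of the two-sided 95% CI for RZZYL minus mometasone lies above −9.5 points in both the Full Analysis Set and the Per Protocol Set, then test superiority in fixed sequence. Say what role the HECSI and NRS scores then have. Restate the power as about 91%, 53% and 16% at true advantages of 20.5, 10 and 0 points with 53 per arm.

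**(b) Keep the HECSI score and/or NRS as primary.** Justify a margin on that scale, compare the 95% CI limit with it, and restate the power that 53 evaluable patients per arm gives under a stated SD.

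On either route, state that a non-significant difference test is not evidence of noninferiority.

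**Cost.** Route (a) is wording only, with no added patients or visits, but the disclosed power is less favourable. Route (b) is also wording at first, but may show that the sample is too small. With no true difference, 90% power needs 2 × 10.507/0.5² ≈ 85 per arm for a margin of 0.5 SD, and 2 × 10.507/0.3² ≈ 234 for 0.3 SD (both margins are assumed for scale).

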### Quality Control

Prior to the commencement of the trial, all participating researchers will receive standardized training on diagnostic interviews to ensure familiarity with the management process and to clarify the implementation procedures. During the trial, 2 clinical physicians will evaluate CHE. The allocation will be fixed, and migration between groups will not be permitted. The reason for a participant’s withdrawal from the study will be documented if they discontinue treatment.

### Ethical Considerations

#### Ethics Approval

Ethics committee, Guang’anmen Hospital China Academy Of Chinese Medical Sciences, China.

#### Ethics and Dissemination

The trial will be carried out in line with the World Medical Association’s Declaration of Helsinki and the legislation and guidelines on Good Clinical Practice established in China. This protocol has been approved by the Ethics Committee of Guang’anmen Hospital, China Academy of Chinese Medical Sciences (2024‐262-KY), and registered on the International Traditional Medicine Clinical Trial Registry Platform (ITMCTR2025000287). Researchers must thoroughly inform participants regarding the study’s purpose, procedures, potential risks, and compensation. Participants will complete 2 informed consent forms: one for their records and the other for the researchers, to be included in the clinical research documentation for future reference.

To express gratitude to participants for their investment of time and transportation costs, and by the ethical committee’s guidance on reasonable compensation (based on local standards for volunteer participation in research and minimum wage rates), participants will receive a subsidy of 200 RMB (approximately US $27.64) upon the completion of the entire treatment and follow-up. This compensation adheres to ethical guidelines for reimbursement, aiming to avoid undue inducement while ensuring fairness. Participants’ privacy and confidentiality will be rigorously protected throughout the study. When the study results are published, participants’ names will be replaced with a unique serial number and the initials of their names to ensure that personal information is not disclosed. Data handling will comply with applicable data protection regulations, and access to personal information will be restricted to authorized researchers.

